## Methods/Design

### Study design

The process of allocation to the two housing programs was determined by needs analyses conducted by the case workers who engaged with homeless individuals in the designated catchment area of inner Sydney. Given this process, a control group was not a feasible option and an ecological study was selected which utilised a longitudinal, mixed methods design. Housing and health outcomes were compared at baseline and 12 months follow-up of the scatter site (Platform 70) and congregated site (Common Ground) programs. The methodology, conduct and reporting of this study is in accordance with the Strengthening the Reporting of Observational Studies in Epidemiology (STROBE) initiatives for cohort studies ([32] STROBE checklist can be found in Additional file 1).

This study encompasses three sources of data collected at baseline and 12 months follow-up: 1) client surveys; 2) semi-structured interviews with clients and stakeholders; and 3) housing and support program data.

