To reduce loss at follow-up, a systematic process for locating and communicating with participants for the follow-up survey was implemented (see Additional file 3). With their consent, at baseline participants filled out a Locator Form asking them for their primary contact information (e.g., phone number, mailing address, email address) and the contact information for family, friends or service providers with whom they have regular contact. The form provided space for participants to note down any specific instructions for contacting them or their nominated contacts. Participants were also asked to sign a Release of Information Form, which provided consent for the researchers to obtain their contact details from Centrelink (a government agency responsible for welfare payments) if other methods of follow-up were not successful. This form provided space for participants to record their Centrelink client identification number to facilitate record access and matching. Signing the Locator and Release of Information forms were voluntary and a decision not to sign either form did not exclude participants from being involved in the research.

In total, 80 participants were recruited at baseline, which equated to a recruitment rate of 66% (Platform 70: 45 of 70 clients recruited, 64%; Common Ground: 35 of 52 clients recruited, 67%). Reasons for non-recruitment included refusal, unable to make contact, non-English speaking, incarcerated and away during the recruitment timeframe. Baseline data collection occurred from November 2012 to May 2013. As shown in Table 1, the demographic compositions of the two samples are mostly similar to that of all clients within the programs.

**Table 1 Tab1:** **Demographic composition of the client survey samples recruited at baseline compared to the overall populations**

**Demographics**	**Platform 70 (scatter site)**		**Common Ground (congregated site)**	
	**Sample (n = 45)**	**Population (N = 70)**	**Sample (n = 35)**	**Population (N = 52)**
Sex (% male)	84	83	77	77
Mean age (years)	44	43	44	44
% Indigenous	20	28	10	14
% born in Australia	82	86	73	74

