For the 12-month follow-up survey, the participant retention rate was 79% (Platform 70: 37 of 45 participants, 82%; Common Ground: 26 of 35 participants, 74%), which is comparable with longitudinal studies of Housing First programs internationally [29,35]. Follow-up surveys were conducted from October 2013 to May 2014. Nine baseline Platform 70 participants did not complete the follow-up survey due to not being contactable (n = 6), refused (n = 2) or incarcerated (n = 1). Similarly, nine baseline Common Ground participants did not complete the follow-up survey due to not being contactable (n = 6), refused (n = 1), incoherent (n = 1) or passed away (n = 1).

The following measures were collected at both baseline and 12-month follow-up surveys, with the exception of some demographic variables that would not change over time (e.g., sex). To maximise the sample sizes, all eligible Platform 70 and Common Ground clients were invited to participate in the client survey, and recruitment continued until all eligible clients had either provided consent or a reason for non-participation in the research had been ascertained.

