### Demographics

Demographic data included sex (male/female), age (years), Indigenous status (yes/no), completed Grade 10 (yes/no), in a relationship (yes/no), number of children, currently employed (yes/no) and cognitive impairment (yes/no). Cognitive impairment was measured using the Montreal Cognitive Assessment (MoCA), which is a standardised screening tool that has been shown to be appropriate for individuals with varying cultural backgrounds, ages and educational levels [36]. Scores range from 0 to 30, with a score of 25 or less indicating a cognitive impairment.

Homelessness and housing history data measures included whether participants had ever experienced the following states of homelessness (yes/no), the total time in each state (12 months or less/more than 12 months), and the age that they first experienced each homelessness state (years): slept rough; emergency accommodation (up to three months); medium to long term accommodation (12 to 24 months); couch surfed; boarding houses or hostels; or in a caravan (other than a holiday). Participants were also asked to quantify how many different periods they had slept rough for six months or more. Lastly, at both baseline and follow-up client surveys, interviewers assisted participants to fill out a housing calendar for the preceding 12 months, which included the type of accommodation and duration of each stay.

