### Service utilisation

To measure health service utilisation, participants were asked if they had attended the following services over the past 12 months (yes/no): inpatient hospital services for physical health; inpatient hospital services for mental health; emergency department (ED) for physical health; ED for mental health; ambulance call-out; drug and alcohol treatment facility; general practitioner (GP) for physical health; GP for mental health; or a specialist mental health service. From this, the total number of different health services utilised over the past 12 months was computed (range 0–8). Participants were asked to report the number of days they had utilised each health service over the past 12 months (range 0–365 days). For example, ‘*In the past 12 months, how many days in total did you stay in hospital because of a physical health problem*?’

Finally, to measure criminal justice system contact, participants reported whether they had been in contact with the following channels of the justice system over the past 12 months (yes/no): held in an adult prison; held overnight by police; attended court for a criminal matter; under supervision of a Parole or other Justice Officer; or stopped by police on the street. From this, the total number of different criminal justice system channels participants had been in contact with over the past 12 months was computed (range 0–5). Participants also reported the number of days over the past 12 months they had contact with each criminal justice system channel (range 0–365 days).

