A detailed examination of mainstream services will utilise the health and criminal justice system contact data collected in the client surveys. Associated costs incurred in the 12 months prior to the baseline client survey will be compared with the cost of services used in the 12 months prior to the follow-up client survey. The cost of health and justice services will also be compared with the NSW population average.

The cost of health and justice services used by client survey participants will be estimated by applying the unit cost for each service to reported use. Unit costs will be estimated from publicly available information including the Report on Government Services 2013 [42] and various other reports, including those published by the Australian Institute of Health and Welfare [43-47]. These sources will also be used to estimate average service use and associated cost for the NSW population.

The cost of delivering the Platform 70 and Common Ground programs will be examined with reference to recurrent expenditure for the period in which clients were housed in the program. We shall also consider the range of rental subsidies provided to clients in the two housing models. Funding and expenditure data will be sought directly from the providers of social, health and tenancy management, and administrative services. To estimate the recurrent cost incurred by housing providers to manage and maintain properties, we shall draw on estimates obtained from the Report on Government Services [42]. Platform 70 and Common Ground case workers potentially provide more time to resolving issues associated with their tenancies than is normal. This implies that the average recurrent cost/dwelling is likely to represent a conservative estimate of the cost incurred by housing providers.

Housing providers also incur the capital cost of accommodation. In our cost analysis we will only consider public and community housing capital costs in the Common Ground program as Platform 70 involves the head leasing of privately owned dwellings. The average capital value of public housing and community housing properties available to Common Ground clients will be established and the annualised value of capital employed estimated by applying an opportunity cost of capital of 8% [42] to the average capital value.

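### Every October 2013 follow-up fell less than 12 months after its baseline, so the 12-month look-backs overlap for those clients and the same days can count in both 'before' and 'after'

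*Protocol article*

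**What the plan says.** The Study design section of the protocol article sets the comparison at two time points: "Housing and health outcomes were compared at baseline and 12 months follow-up". The Client surveys section gives the fieldwork months: "Baseline data collection occurred from November 2012 to May 2013", and then "Follow-up surveys were conducted from October 2013 to May 2014".

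Several outcomes are collected over the year before each survey:

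- **Treatment** (Health section): for each reported condition, whether it was treated in the last 12 months, yes or no.
- **Health service use** (Service utilisation section): "Participants were asked to report the number of days they had utilised each health service over the past 12 months (range 0–365 days". Yes/no items and a count of different services use the same period.
- **Justice contact** (same section): yes/no items, a count of channels and days of contact, again over 12 months.
- **Housing** (Demographics section): at both surveys, "interviewers assisted participants to fill out a housing calendar for the preceding 12 months", with the type and length of each stay.
- **Cost** (Data analysis section): the year before baseline is set against the year before follow-up: "Associated costs incurred in the 12 months prior to the baseline client survey will be compared with the cost of services used in the 12".

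The article gives no individual intervals and does not mention overlapping look-backs.

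**The concern.** A before-after comparison of two yearly totals is easy to interpret only if the years share no days. When a client is followed up before a full year has passed, the follow-up look-back reaches behind the baseline survey. A hospital stay, a prison spell or a period of rough sleeping in that stretch is then reported at both surveys. It counts as 'before' and again as 'after'.

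The outcomes exposed to this serve Aim 1 (change in housing stability, treatment, and health and justice contact) and Aim 3 (the cost offset). The expected direction is towards no change, so a real fall in service use or cost would tend to look smaller than it was.

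**Working it through.** **Inputs.** Baseline window: November 2012 to May 2013. Follow-up window: October 2013 to May 2014 (both from the Client surveys section). Only months are given, so I take the first and last days of the months as outer bounds. The look-back is 12 months, or 365 days. Completers number 37 + 26 = 63 of 80, and 63/80 = 78.75%, which reproduces the stated 79%.

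**Step 1: can the stated 12 months hold for all clients?** The interval is the follow-up date minus the baseline date. The overlap is 365 minus the interval when the interval is below 365; the gap is the interval minus 365 when it is above.

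| Baseline | Follow-up | Interval (days) | Overlap or gap |
|---|---|---|---|
| 1 Nov 2012 | 31 Oct 2013 | 364 | overlap 1 day (0.3% of 365) |
| 1 Nov 2012 | 1 Oct 2013 | 334 | overlap 31 days (8.5%) |
| 30 Nov 2012 | 1 Oct 2013 | 305 | overlap 60 days (16.4%) |
| 31 May 2013 | 31 May 2014 | 365 | none |

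The first row is the longest interval that any October 2013 survey can have. It is below 365 days, so every October 2013 follow-up overlaps by at least one day, whatever the individual dates. The last row shows that the windows end exactly a year apart, so no client need have exceeded 12 months.

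**Step 2: outer bounds.** Pairing the last possible baseline with the first possible follow-up (31 May to 1 October 2013) gives 123 days. Pairing the first baseline with the last follow-up (1 November 2012 to 31 May 2014) gives 576 days, a gap of 576 − 365 = 211 days. These are limits set by the calendar, not estimates.

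**Step 3: what an overlap of k days does to a total.** The baseline total is the first 365 − k days of the baseline year plus the k shared days. The follow-up total is the same k shared days plus the 365 − k days after baseline. In the difference the shared days cancel, leaving 365 − k days against 365 − k days, although the result is read as a full year's change. If the rate is constant at r0 before the baseline survey and r1 after it, the measured change is (365 − k)(r1 − r0), which is interval/365 times the full-year change:

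- 364 days: 364/365 = 0.997
- 334 days: 334/365 = 0.915
- 305 days: 305/365 = 0.836

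For yes/no items the loss is not proportional: one event in the shared days can score yes at both surveys.

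**Step 4: which outcomes are spared.** The BSI looks back seven days, the WHOQOL-BREF two weeks, and recent substance use three months. The shortest possible interval is 123 days, so none of these overlaps.

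**The case against.** The strongest reply is that only the overlap for October 2013 surveys is proven, and that it may be trivial. It could be as little as one day, for an unknown number of clients. Windows of seven and eight months fit a follow-up that kept baseline order and started about a month early. This stands, and it limits the size of the point.

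The factor interval/365 also assumes that rates change at the baseline survey. That survey is not the start of housing: the programs opened in August and November 2011, and the eligibility criteria admit clients already housed as well as those waiting. A client housed before baseline has housed time in the 'before' year, so the loss need not equal k/365. This stands too; the factors in the working are illustrations.

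Models and visit windows may be set out in a fuller document that is not shown, so silence on adjustment for interval is no fault in itself. But no such document can place an October 2013 survey 12 months after a baseline in November 2012 or later. Program records of days housed and housing transitions do not depend on survey recall, which narrows the reach for housing outcomes.

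A reader might infer more than the documents support:

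- **That some clients have months covered by neither survey.** The dates allow this but also fit a schedule with no gap.
- **That intervals ran as short as 123 or as long as 576 days, or that change is diluted by a quarter or more.** Nothing shows that such pairings occurred.
- **That the distortion differs between programs or by how hard clients were to trace.** No intervals are given by client or program.

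**Conclusion.** The point holds in a limited form. By the article's own months, every October 2013 follow-up came at most 364 days after baseline, so the 12-month label is wrong for those clients and their look-backs overlap. This affects treatment, service use, justice contact, the housing calendar and the cost comparison, mainly towards no change. Later follow-ups may be affected as well.

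The number of clients involved and the overall size cannot be determined from the article. If follow-up kept baseline order about a month early, the overlap is roughly 0 to 9% of the look-back year (31/365 = 8.5%), reaching 60/365 = 16.4% for a client seen at the end of November 2012 and again on 1 October 2013. The existence of the overlap rests only on the stated months and a look-back counted from each survey date. Turning it into a percentage loss of effect also requires constant rates that change at baseline, which the documents do not establish.

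**What to change.** 1. Derive each client's baseline-to-follow-up interval from the survey dates and report its distribution by program.
2. Cut the follow-up housing calendar at the baseline date and express housing outcomes per day after baseline. The recorded length of each stay makes this possible.
3. Keep all completers in the main comparison of service use, justice contact and cost. Add a sensitivity analysis that excludes clients with overlapping look-backs or, for day counts and costs only, scales for the overlap with the assumption stated. Scaling does not suit yes/no items or counts of different services.
4. Replace the 12-month description with the actual range of intervals, or correct the fieldwork dates if they are misprinted.

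I would not make clients with at least 365 days the primary set. With 63 completers, that would drop a client seen on day 364 and could remove many others if follow-up ran slightly early.

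The cost is one derived variable and an additional, less precise sensitivity analysis. No new data collection is needed, provided the survey dates were kept.

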### Demographics

Demographic data included sex (male/female), age (years), Indigenous status (yes/no), completed Grade 10 (yes/no), in a relationship (yes/no), number of children, currently employed (yes/no) and cognitive impairment (yes/no). Cognitive impairment was measured using the Montreal Cognitive Assessment (MoCA), which is a standardised screening tool that has been shown to be appropriate for individuals with varying cultural backgrounds, ages and educational levels [36]. Scores range from 0 to 30, with a score of 25 or less indicating a cognitive impairment.

Homelessness and housing history data measures included whether participants had ever experienced the following states of homelessness (yes/no), the total time in each state (12 months or less/more than 12 months), and the age that they first experienced each homelessness state (years): slept rough; emergency accommodation (up to three months); medium to long term accommodation (12 to 24 months); couch surfed; boarding houses or hostels; or in a caravan (other than a holiday). Participants were also asked to quantify how many different periods they had slept rough for six months or more. Lastly, at both baseline and follow-up client surveys, interviewers assisted participants to fill out a housing calendar for the preceding 12 months, which included the type of accommodation and duration of each stay.

### Health

To measure general health, participants reported whether they had ever been diagnosed with the following physical or mental health conditions (yes/no): asthma; emphysema, bronchitis or other respiratory disease; epilepsy or seizure; diabetes; cancer; high blood pressure; stroke; any other heart or circulatory condition; blood-borne virus; liver disease; cellulitis; skin condition; arthritis or joint/muscle disease; eye/vision problems that cannot be corrected by glasses; dental problems; chronic pain; mood disorder; anxiety disorder; psychotic disorder; substance use disorder; personality disorder; eating disorder; or impulse-control disorder. When a health condition was reported, participants were asked if they had received treatment for that condition in the past 12 months (yes/no).

Psychological symptom patterns were measured using the Brief System Inventory (BSI; [37]), a 53-item self-report inventory in which participants rated the extent of distress caused in the past seven days by various symptoms on a five-point Likert scale (‘not at all’, ‘ a little bit’, ‘moderately’, ‘quite a bit’, ‘extremely’). Nine primary symptom dimensions were measured (somatisation, obsessive-compulsive, interpersonal sensitivity, depression, anxiety, hostility, phobic anxiety, paranoid ideation and psychoticism) to provide information on individuals’ psychological status and symptomatology. An overall index of mental health functioning was also generated (Global Severity Index; [37]). The BSI has been used as a valid measure of psychological symptomatology with homeless and vulnerable populations [17,38] and is sensitive to identifying change over time [39,40].

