### Aims

While the Housing First approach has been evaluated internationally [27,20,28,29] and is being keenly applied in Australia, there has been a paucity of evidence on the effectiveness of Australian adaptations of the approach. Findings from evaluations of individual Housing First programs within Australia have recently been released publicly [30,31], however no study examining more than one of these adaptations with the same methodology has been conducted. Further, evaluations to date have focused largely on housing sustainability rather that incorporating broader measures of health and quality of life. Given this, there remains a pressing need to determine the efficacy of these respective models (Platform 70 [scatter site]; Common Ground [congregated site]) in relation to both housing and health outcomes. In response to this gap in the evidence-base, we have commenced a longitudinal analysis of these two adaptations using a standardised mixed methods approach to examine the changes in housing and health outcomes associated with the respective models.

Specifically, we aim to:Determine whether changes occurred with respect to clients’ housing stability, physical and mental health and treatment rates, psychological distress, quality of life, substance use patterns, and health and criminal justice system contact.Identify the demographic and social characteristics of clients that predicted success in each model. For the purposes of this study, success was defined as sustained tenancy and improved health and well-being outcomes.Calculate the net of ‘cost offsets’ of the two programs; that is, the reduction in measurable health, criminal justice and other costs borne by government as a consequence of the program.

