### Substance use

Substance use patterns were measured by a number of variables. Lifetime and three-month use of the following substances was recorded (yes/no): tobacco; alcohol; cannabis; amphetamines; cocaine; inhalants; sedatives; hallucinogens; and opioids. Those participants who reported use in the past three months were asked to indicate their frequency of use (once weekly or less/more than weekly), the frequency they had a strong desire or urge to use each substance (once weekly or less/more than weekly), and the frequency that health, social, legal or financial problems resulted from the use of each substance (once monthly or less/more than monthly). Non-medical use of a drug by injection in lifetime (yes/no) and the past three months (yes/no) was recorded. If participants had injected in the past three months, they were asked to rate their frequency of injecting (once weekly or less/more than weekly).

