### Data analysis

Given the nature of the housing programs under evaluation, we were limited by the number of clients engaged with each program and therefore did not perform a formal power-based sample size calculation. Instead, we invited all eligible Platform 70 and Common Ground clients to participate in the client survey, and recruitment continued until all eligible clients had either provided consent or declined participation in the research.

Loss to follow-up comparisons that assesses the characteristics of participants in the two programs who completed both baseline and follow-up client surveys (completers) against those who only completed the baseline survey (non-completers) will be made. The purpose of these comparisons is to determine whether there are any key differences between survey completers and non-completers of each program. Other patterns of missing data will be examined to determine if there are potential biases. Appropriate literature that addresses how to deal with missing data and small populations and/or small samples will also be consulted.

To address Aims 1 and 2, a profile of clients engaged with the two housing programs will be constructed, which will include demographics, homelessness history and health status. Multivariate analysis will be undertaken to determine changes over time (baseline to follow-up) in key outcomes, including housing, health status and treatment rates, quality of life, substance use patterns, and contact with the health and criminal justice systems within and across the two programs. Additionally, multivariable logistic regression will be used to identify factors associated with sustained tenancies using SAS version 9.4 software.

Qualitative interviews with clients and stakeholders will be thematically analysed in line with the general inductive approach using NVivo 10 software. The analysis will identify key themes in sustained and failed tenancies. These data will be presented in such a way as to give some indication of the commonality or otherwise of particular views, but will not purport to be representative.

To address Aim 3, the cost to government of mainstream health and criminal justice service use by Platform 70 and Common Ground clients and how this use changed over time will be examined. It will also review the cost of delivering the programs and the extent to which this is offset by a decrease in the cost of mainstream government services use by participants.

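### Change in health status rests on lifetime diagnoses, which cannot show improvement, and a treatment rate taken among reporters at each survey would compare different groups

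*Protocol article*

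**What the plan says.** All places are in the protocol article.

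- **Health.** For general health, "participants reported whether they had ever been diagnosed with the following physical or mental health conditions (yes/no"). The list has 23 entries, 16 physical and 7 mental. Treatment is a follow-on question: "When a health condition was reported, participants were asked if they had received treatment for that condition in the past 12 months (yes/no"). No item asks whether a condition is still present.
- **Client surveys.** "The following measures were collected at both baseline and 12-month follow-up surveys, with the exception of some demographic variables that would not change over time". No different wording is given for the follow-up survey.
- **Aims.** Aim 1 looks for change in housing stability and in "physical and mental health and treatment rates, psychological distress, quality of life, substance use patterns, and health and criminal justice system contact". Aim 2 counts better health as part of success.
- **Data analysis.** "Multivariate analysis will be undertaken to determine changes over time (baseline to follow-up) in key outcomes, including housing, health status and treatment rates". The comparison is to be made both within each program and between the two.
- **Abstract, Methods/Design.** Health status and treatment rates are among the factors expected to improve once housing is stable.
- **Health and Quality of life.** The BSI covers the past seven days. The WHOQOL-BREF covers the past two weeks and has physical and psychological domains.

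**The concern.** An item about ever having been diagnosed records history, not current state. A person who truthfully answers yes at baseline must answer yes a year later, whether or not the condition has resolved. The only real movement is from no to yes. An outcome expected to improve is therefore measured by something that can only stay level or get worse.

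The movement may also carry information about the programs. Common Ground has health services on site, and Platform 70 clients receive support around the tenancy. More contact with care plausibly means more conditions found. A program that succeeds in connecting clients to care could then appear to harm their health. If detection differs between the two models, the comparison between programs is affected too.

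Treatment has a related difficulty. Treatment data exist only for people who report the condition at that survey. If the rate is computed among reporters at each wave, the follow-up group includes newly diagnosed people who were not in the baseline group, and the two rates describe different people.

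**Working it through.** **Inputs from the article.** Follow-up was completed by 37 of 45 Platform 70 and 26 of 35 Common Ground participants. These give 37/45 = 82.2%, 26/35 = 74.3% and (37 + 26)/80 = 63/80 = 78.75%, matching the stated 82%, 74% and 79%. The article gives no prevalence, treatment rate or incidence for any condition.

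**What the item can show.** For one person and one condition, a truthful pair of answers is no/no, no/yes or yes/yes. The pair yes/no is not available. Across all 23 items the largest real improvement is therefore zero.

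**Assumed illustration.** Take one condition among 63 completers, with 30 ever diagnosed at baseline and 15 of these treated in the past 12 months. Treatment among those 30 does not change. Let *k* be the number of new diagnoses by follow-up.

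- Share ever diagnosed = (30 + *k*)/63
- Treatment rate among reporters, all new cases treated = (15 + *k*)/(30 + *k*)
- Treatment rate among reporters, no new case treated = 15/(30 + *k*)
- Treatment rate among baseline reporters = 15/30

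| *k* | Ever diagnosed | Rate, all new treated | Rate, no new treated | Rate, baseline reporters |
|---|---|---|---|---|
| 0 | 30/63 = 47.6% | 15/30 = 50.0% | 15/30 = 50.0% | 50.0% |
| 3 | 33/63 = 52.4% | 18/33 = 54.5% | 15/33 = 45.5% | 50.0% |
| 6 | 36/63 = 57.1% | 21/36 = 58.3% | 15/36 = 41.7% | 50.0% |
| 9 | 39/63 = 61.9% | 24/39 = 61.5% | 15/39 = 38.5% | 50.0% |

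The rate among reporters moves up or down according to how many new cases are treated, while nothing changes among those already diagnosed.

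**Recovery.** Suppose instead that 6 of the 15 treated people recover and stop treatment. The ever-diagnosed share stays at 30/63 = 47.6%, and the treatment rate falls from 50.0% to 9/30 = 30.0%. Neither figure shows the improvement.

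**Ways the observed share could fall.** If 5% to 10% of the 30 fail to repeat their earlier answer, the share becomes 28.5/63 = 45.2% to 27/63 = 42.9%. It could also fall if all 80 at baseline were compared with the 63 completers and those lost had more diagnoses. Neither fall is better health.

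**The case against.** **Health status is not defined for the change analysis.** The BSI is described under Health, and the Data analysis section does not list psychological distress separately, so health status there may well include it. The same section also uses health status for the client profile, which suits lifetime diagnoses. This has force for mental health. It has less for physical health: quality of life, and with it the WHOQOL-BREF physical domain, is listed as its own outcome in both Aims and Data analysis. Aim 1 also separates distress from physical and mental health. The diagnosis list is then the stated measure of physical health status.

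**Improvement can still be shown elsewhere.** A reader might infer that the study cannot test whether health improves. The documents do not support that. The BSI and the WHOQOL-BREF describe current state and are collected at both waves. The article also describes the BSI as able to pick up change over time.

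**The denominator is not stated.** A reader might infer that treatment rates will be computed among reporters at each wave, and that any rise would be an artefact. The article gives only the skip rule. A rate over all participants or over baseline reporters can be computed from the same data, and an analysis plan could settle the choice. The shift can go either way. A rise may also reflect real events: if six people are newly diagnosed and treated, those treated go from 15/63 = 23.8% to 21/63 = 33.3% of the sample, which may be better access to care. So this part holds only as a conditional warning.

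**Substance use.** A reader might see the same fault in the frequency item, since "Those participants who reported use in the past three months were asked to indicate their frequency of use". But use in the past three months is recorded as yes or no for each listed substance, so stopping is captured. Nothing says that frequency will be analysed among users alone. No finding arises there.

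**Detection may have begun before baseline.** Clients had outreach support before entering either program, and some were already housed at baseline. Some new diagnoses may therefore predate the first survey. This bears on the size of the rise, not on the item's inability to fall.

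**Conclusion.** The point holds. A correctly answered lifetime diagnosis cannot show improvement in the same person. Read as a change outcome, it would turn better detection into apparent deterioration. This follows from the wording of the item and its repetition at both surveys, and needs no assumed figures.

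For treatment rates the conclusion is conditional. If the rate is taken among reporters at each wave, new diagnoses alone can shift it. In the illustration, six new cases move it from 50.0% to anywhere between 41.7% and 58.3%. The counts of 30 diagnosed, 15 treated and 3 to 9 new cases are assumptions; only the 63 completers come from the article. That better access to care would raise diagnoses is plausible but not quantified in the article.

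The severity is moderate. Current-state measures are already collected, the article names no primary outcome that rests on the diagnosis list, and the one named regression concerns sustained tenancies.

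**What to change.** In the Data analysis section:

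1. Use lifetime diagnoses only for the baseline profile and as covariates.
2. Base change in health status on the BSI Global Severity Index and the WHOQOL-BREF physical and psychological domains.
3. Compute change in treatment rate as a paired comparison among participants who reported the condition at baseline. State how those who do not report it again at follow-up are handled, because the skip rule leaves them without a treatment answer.
4. Report new diagnoses separately, as detection.

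This changes analysis wording only and needs no new data. The cost is smaller paired denominators, most noticeable for rare conditions. One limit remains: with no item on current status, a fall in treatment among baseline reporters cannot be separated into recovery and loss of care, and the report should say so.
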